# Medicinal Cannabis (MedCan 3): a randomised, multicentre, double-blind, placebo-controlled trial to assess THC/CBD (1:20) to relieve symptom burden in patients with cancer—a study protocol for a randomised controlled trial

**DOI:** 10.1186/s13063-024-08091-z

**Published:** 2024-05-01

## Abstract

**Background:**

Distressing symptoms are common in advanced cancer. Medicinal cannabinoids are commonly prescribed for a variety of symptoms. There is little evidence to support their use for most indications in palliative care. This study aims to assess a 1:20 delta-9-tetrahydrocannabinol/cannabidiol (THC/CBD) cannabinoid preparation in the management of symptom distress in patients with advanced cancer undergoing palliative care.

**Methods and design:**

One hundred and fifty participants will be recruited across multiple sites in Queensland, Australia. A teletrial model will facilitate the recruitment of patients outside of major metropolitan areas. The study is a pragmatic, multicenter, randomised, placebo-controlled, two-arm trial of escalating doses of an oral 1:20 THC/CBD medicinal cannabinoid preparation (10 mg THC:200 mg CBD/mL). It will compare the efficacy and safety outcomes of a titrated dose range of 2.5 mg THC/50mgCBD to 30 mg THC/600 mg CBD per day against a placebo. There is a 2-week patient-determined titration phase, to reach a dose that achieves symptom relief or intolerable side effects, with a further 2 weeks of assessment on the final dose.

The primary objective is to assess the effect of escalating doses of a 1:20 THC/CBD medicinal cannabinoid preparation against placebo on change in total symptom distress score, with secondary objectives including establishing a patient-determined effective dose, the effect on sleep quality and overall quality of life. Some patients will be enrolled in a sub-study which will more rigorously evaluate the effect on sleep.

**Discussion:**

MedCan-3 is a high-quality, adequately powered, placebo-controlled trial which will help demonstrate the utility of a THC:CBD 1:20 oral medicinal cannabis product in reducing total symptom distress in this population. Secondary outcomes may lead to new hypotheses regarding medicinal cannabis’ role in particular symptoms or in particular cancers. The sleep sub-study will test the feasibility of using actigraphy and the Insomnia Severity Index (ISI) in this cohort. This will be the first large-scale palliative care randomised clinical trial to utilise the teletrial model in Australia. If successful, this will have significant implications for trial access for rural and remote patients in Australia and internationally.

**Trial registration:**

ANZCTR ACTRN12622000083796. Protocol number 001/20. Registered on 21 January 2022. Recruitment started on 8 August 2022.

**Supplementary Information:**

The online version contains supplementary material available at 10.1186/s13063-024-08091-z.

## Introduction

Patients with advanced cancer report many disabling symptoms. Traditionally, the efficacy of palliative interventions has been evaluated by measuring their effect on a specific symptom. For example, the intervention of oral haloperidol is said to be an efficacious palliative intervention as it provides a statistically significant and clinically relevant reduction in nausea.

Medicinal cannabis (MC) has not demonstrated consistent efficacy for any particular symptom in the palliative care of patients with advanced cancer. This has not reduced public support for its use. Consumers perceive the potential benefit as a holistic one that helps them ‘feel better’ overall, without specifically impacting on an individual symptom.

The value of aligning outcome measures with what consumers consider important is increasingly recognised. This is especially the case for MC research, as consumers often have strongly held, well-articulated preconceptions of how MC should be used [1].

There is little high-quality evidence for MC in palliative care generally. There are even fewer high-quality trials assessing the role of MC in reducing total symptom burden in these patients, rather than assessing individual symptoms, e.g. pain or nausea [2]. Moreover, which particular cannabinoid or cannabinoid combination works best for symptom management is still yet to be determined. Our team has recently completed a randomised clinical trial (RCT) of cannabidiol (CBD) as a single agent, showing no reduction in total symptom burden compared to placebo [3]. A subsequent RCT is assessing a 1:1 THC/CBD preparation [4]. The present study will clarify whether another THC/CBD combination, namely a 1:20 THC/CBD oral preparation, will reduce the total symptom burden in advanced cancer. Both clinicians and consumers seem to suspect a benefit to sleep symptoms, and so, we are deliberately assessing sleep symptoms in a separate sub-study to see whether there is a benefit in this particular patient population [5].

## Ethics

Research ethics approval has been obtained from all participating sites—Mater Misericordiae Ltd Human Research Ethics Committee, HREC/MML/81780, and St Vincent’s Health and Aged Care Human Research and Ethics Committee, HREC_22-02_PGOO. All participants give written informed consent, and the study is conducted in accordance with the Good Clinical Practice guidelines.

## Methods

### Aims and objectives

The objective is to determine whether medicinal cannabinoids have a role in reducing symptoms in patients with advanced cancer who are receiving palliative care. We hypothesise that participants in the MC arm will experience a greater reduction in symptom distress than those in the placebo arm.

The primary objective is to define whether self-titrated increasing doses of a 1:20 THC/CBD oral suspension formulation will reduce a patient’s total symptom distress score (TSDS) more than a placebo at day 14. TSDS is the sum of all components on the nine-item Edmonton Symptom Assessment Scale (ESAS) [6].

Secondary objectives include (a) ascertaining the median dose of 1:20 THC/CBD formulation achieved when patients are asked to titrate to effect or tolerance within a pre-specified range; (b) describing MC-induced change in individual symptom scores at days 7, 21 and 28; and (c) assessing the change in total physical and emotional scores, global impression of change, anxiety and depression and sleep quality.

#### Study design

This is a pragmatic, multicentre, randomised, placebo-controlled, two-arm parallel trial of escalating doses of oral THC/CBD: 10 mg:200 mg/mL oral solution. Participants will self-titrate the dose over the first 14 days using a pre-defined dosing schedule. They will cease self-titration at the maximum day 14 dose or at that dose which relieves symptoms or is limited by adverse effects. This dose will be continued for a further 2-week period for documentation of any benefits and adverse effects. This study design is based on previous RCTs successfully undertaken by this group [3, 4, 7].

#### Study setting

Participants will be recruited from sites within the Queensland Palliative Care Research Group (QPCRG) in metropolitan Brisbane. Additionally, we will be offering patients in more rural and remote areas the ability to participate by utilising a teletrial model. In this model, local research nurses employed by a government-funded teletrial network will provide on-the-ground support to health professionals based in Mater Hospital Brisbane. Potential participants outside metropolitan areas will be reviewed by an on-site teletrial research nurse in person. These nurses will perform all eligibility assessments on-site with remote supervision. If eligible, trial medications will be couriered to the patient. Similarly, actigraphs will be couriered to patients who wish to enrol in the sleep-related sub-study described below. It is anticipated that this will be predominately an outpatient study (although inpatients are still eligible), with sites having the ability to access this participant population from their established clinical service.

All participants will be given standard palliative care according to the local practice of the recruiting centre. They will continue all current medications including opioids, antiemetics, sedatives and specific anti-cancer therapy (including chemotherapy, immunotherapy and radiotherapy).

#### Study participants

Patients are eligible if they have the following:An advanced histologically proven cancer diagnosis (metastatic or locally advanced)Ongoing review by a palliative care teamAn ESAS total symptom distress score (TSDS) of ≥ 10/90 for cancer-related symptoms with at least one ESAS individual score ≥ 3/10A performance status of ≥ 30/100 as measured by the Australia-modified Karnofsky Scale (AKPS)A negative THC urine test at the eligibility assessmentThe ability to swallow oral medicationsAre aged ≥ 18 years, English-speaking (or have an interpreter available)

Where applicable, potential participants must:Submit a urine sample to exclude pregnancy (female patients of reproductive potential)Agree to avoid pregnancy for the duration of the trial and 3 months after ceasing the study medication (female patients of reproductive potential)Agree to avoid fathering a child for the duration of the trial and three months after ceasing the study medication (male patients)Agree to avoid sperm donation for the duration of the trial and 3 months after ceasing the study medication (male patients)Agree not to drive any motor vehicle for the duration of the trial

Potential participants will be excluded if they have:A history of hypersensitivity to any cannabinoidUnstable, untreated cardiovascular diseaseSevere hepatic impairment (total bilirubin ≥ 1.5 times the upper limit of the normal range), aspartate aminotransferase (AST) and alanine aminotransferase (ALT) ≥ 3.0 times the upper limit of the normal range (subjects with liver metastases excluded if AST and ALT of ≥ 5.0 times the upper limit of normal)Severe renal impairment (eGFR ≤ 20 mL/min/1.73 m.^2^)A history of psychiatric disorder (severe depression or anxiety, personality disorder, psychosis, schizophrenia and/or suicidal ideation)Cognitive impairment (St Louis University Mental Status Examination (SLUMS) ≤ 20/30)A known substance use disorder (Alcohol, Smoking and Substance Involvement Screening Test (ASSIST) examination scoring > 27) for any substanceA history suggesting drug diversionParticipated in a trial of a new clinical entity within the prior 28 daysTreatment with a new specific anti-cancer agent (chemotherapy, targeted or hormonal therapy) or radiotherapy within the last 7 daysA nut allergyA positive urine test for the presence of THC

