### Randomisation

Eligible patients will be assigned in equal numbers to one of the two arms at random. Random number tables will be used for computer-generated randomisation schedules at an independent location by the staff not otherwise involved in the trial. A central registry will hold treatment allocations as determined by a permuted block randomisation schedule. Each site will have its own block randomisation schedule leading to even allocation to each treatment arm within each site. Actions to minimise the risk of bias are detailed in Additional file 1: Table S1.

Following fully informed written consent, the procedure will be as follows:The research pharmacy will be notified of a new participant.The investigator will complete a trial prescription with the participant’s study ID number and provide this to the trial pharmacy.Based on the randomisation schedule, the pharmacist will dispense the appropriate medication in a bottle labelled ‘THC:CBD 10 mg:200 mg/mL or placebo’.Participant ID, allocation number, date of request, preparation and dispensing will be recorded by the site pharmacist for each instance.

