### Intervention

Trial medication and placebo oil formulation will be provided by Little Green Pharma Ltd. Little Green Pharma is supplying the medication free of charge but has no input into the study design nor execution. They will have no role in the analysis or publication of results.

The intervention arm (arm 1) is an oil formulation of THC/CBD 10 mg/200 mg/mL for oral administration (LG Pharma Pty Ltd.) to be delivered over the dose range of THC:CBD 2.5 mg/50 mg (0.25 mL once daily) to THC:CBD 30 mg/600 mg per day (1 mL three times daily). The placebo (arm 2) is a taste and appearance-matched oil formulation without the active ingredient though otherwise indistinguishable. Both arms will otherwise receive the usual palliative care. No part of usual palliative care is prohibited as part of the trial.

Both active and placebo arms will be provided one 70-mL bottle containing 50 mL of the oil solution. Participants will be instructed to store the bottles at room temperature and away from light. Bottles will have a child-resistant cap. Participants will be educated about how to administer medication via a supplied syringe and how to follow the dosing schedule. They will be instructed to use only those syringes supplied by investigators. Participants will record their dosing in the provided dosing schedule diary. Any product remaining at the conclusion of the trial will be returned to the research officer and destroyed by the local site pharmacy in accordance with pharmacy guidelines. Participants who are enrolled through the teletrial infrastructure will have their trial medicine sent to their local Queensland Health (government) facility for safekeeping until they retrieve it. They will use it in a similar way and then return it to the facility at the end of the trial.

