### Assessments

The research staff will contact all participants twice weekly for the first 2 weeks in addition to outpatient clinic reviews on days 0, 7, 14, 21 and 28, with outcome measures recorded at each of these time points. In addition to clinical documentation, symptom burden will be assessed using the Edmonton Symptom Assessment Scale (ESAS). Documentation of disease status (e.g. response or progression of disease) will be assessed at days 14 and 28.

A routine haematology and biochemistry screen including liver function tests will be taken at eligibility/baseline assessment. Blood for C-reactive protein (CRP) as a basic test of inflammation will be taken at baseline, day 14 and day 28. All consenting participants will have a urine test to confirm no recent use of THC-related products as a pre-screen. Female participants of child-bearing potential will have a urine test to exclude pregnancy. Additionally, patients will receive a phone call from a research nurse twice per week in the first fortnight, and then once per week for the second fortnight. Adverse events will be assessed at all of these interactions.

Participants in the optional sleep sub-study will be assessed using the Insomnia Severity Index (ISI) and Sleep Numerical Scale at days 0, 7 and 14. They will wear an accelerometer on their wrists for 14 days to measure circadian activity, sleep quality and quantity. Actigraphy has been found to be a validated, objective way to measure sleep outcomes [8].

Participants will be contacted at day 56 (+ 4 weeks post-last dose) to assess for adverse events as well as record post-trial cannabinoid use. Death will be noted for all participants up to the census point. This protocol has been written in accordance with the Standard Protocol Items: Recommendations for Interventional Trials (SPIRIT) (Table 1) [9]. A SPIRIT guideline checklist can be found in the supplementary material.

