If the interim analysis shows a significant difference, the investigators and the DSMB will be unblinded to the study groups and make any stopping decision on the basis of the nature of any AEs and/or SAEs and ethical grounds, as well as consideration of any statistical differences between the groups. Grounds for stopping on evidence of clear benefit will be considered. The Peto approach will be taken with symmetric stopping boundaries at *p* = 0.001.

A detailed statistical analysis plan will be prepared and ratified by the DSMB.

The sleep part of the study will be powered to detect a mean difference of ≥ 6 on the ISI between the intervention arm and the placebo group. Assuming a 1:1 ratio of active and placebo treatment, a mean difference between the groups (reduction in ISI score) of ≥ 6, a standard deviation of the difference of 8, alpha of 0.05 and power of 80%, 58 participants, 29 in each group, would be needed. To allow for 20% attrition, 74 subjects (37 in each group) will be recruited.

All protocol modifications will be approved by the relevant Human Research Ethics Committee and communicated to all investigators, and trial registration information updated. All investigators will have access to the final dataset. The datasets used and/or analysed during the study will be available from the corresponding author upon reasonable request.

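### The liver exclusion joins AST and ALT with 'and', so read literally a marked rise in only one enzyme does not exclude; it should say 'AST or ALT' (minor safety wording error)

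*Protocol article*

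**What the plan says.** The hepatic criterion is one item in the exclusion list under Study participants in the Protocol article. It names severe hepatic impairment, gives a bilirubin limit of 1.5 times the upper limit of normal (ULN) in brackets, and then gives the enzyme limit: "aspartate aminotransferase (AST) and alanine aminotransferase (ALT) ≥ 3.0 times the upper limit of the normal range". A further bracket relaxes that limit for one subgroup: "subjects with liver metastases excluded if AST and ALT of ≥ 5.0 times the upper limit of normal". Both enzyme clauses join AST and ALT with 'and'.

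Under Assessments, the tests needed to apply the rule are scheduled: "A routine haematology and biochemistry screen including liver function tests will be taken at eligibility/baseline assessment". Under Study setting, eligibility at teletrial locations is assessed by local research nurses: "These nurses will perform all eligibility assessments on-site with remote supervision". Under Randomisation, an investigator then has to act before drug is dispensed: "The investigator will complete a trial prescription". The top of the dose range, under Intervention, is "THC:CBD 30 mg/600 mg per day (1 mL three times daily").

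**The concern.** In an exclusion list a patient is barred only when the stated condition is met. If the condition is that AST and ALT are both at or above a multiple, one high enzyme with the other just below the limit does not meet it. The rule then works against its purpose, because it admits the patient with the larger single abnormality and bars the patient with two smaller ones.

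This is the only numerical liver-enzyme rule in the article. The sponsor clearly regards liver enzymes as a reason to withhold the drug, and expects patients with liver metastases, since it wrote a separate limit for them. Several sites apply the rule, some through nurses supervised at a distance, so it needs to give the same answer wherever it is read. What is at stake is consistent and safe eligibility, not the statistical properties of the trial.

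**Working it through.** The plan gives no figure to reproduce. The check is one of logic: apply the two possible readings to the same patients and see where they differ.

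**Inputs** (all from Study participants): bilirubin limit 1.5 × ULN; enzyme limit L = 3.0 × ULN, or L = 5.0 × ULN with liver metastases; connector between the enzymes, 'and', in both clauses.

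**Rules compared**, with bilirubin below 1.5 × ULN throughout so that it plays no part:
- Both-enzymes reading: exclude if ALT ≥ L and AST ≥ L.
- Either-enzyme reading: exclude if ALT ≥ L or AST ≥ L.

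The patient values below are illustrative multiples of ULN.

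| Limit L | ALT | AST | Both-enzymes reading | Either-enzyme reading |
|---|---|---|---|---|
| 3.0 | 8.0 | 2.5 | eligible | excluded |
| 3.0 | 3.0 | 2.9 | eligible | excluded |
| 3.0 | 3.0 | 3.0 | excluded | excluded |
| 3.0 | 2.9 | 2.9 | eligible | eligible |
| 5.0 (liver metastases) | 12.0 | 4.5 | eligible | excluded |
| 5.0 (liver metastases) | 5.0 | 5.0 | excluded | excluded |
| 5.0 (liver metastases) | 4.9 | 4.9 | eligible | eligible |

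The readings agree when both enzymes are at or above the limit and when both are below it. They give opposite decisions whenever exactly one is at or above it. Comparing the first and third rows shows the inversion: under the literal reading 8.0 with 2.5 enters, and 3.0 with 3.0 does not.

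**Does other text settle it?** No other section says that either enzyme alone excludes, and no other exclusion covers an isolated enzyme rise. The conjunction appears in two separate clauses, so a single slip is less likely. Elsewhere in the same list alternatives are marked with 'or' or 'and/or' (the psychiatric and the recent anti-cancer treatment items), which gives a reader some ground for taking 'and' at face value.

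**How many patients?** The number affected is the number of otherwise eligible patients with exactly one enzyme at or above its limit and bilirubin below 1.5 × ULN, at sites that apply the literal reading. The documents give neither that frequency nor any site's practice, so the number cannot be derived.

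**The case against.** The strongest reply is that this is loose shorthand and not a wrong rule. Naming both enzymes before one threshold is a common way of saying that each is subject to it. A clinician looking at an ALT of 8 × ULN is unlikely to enrol the patient because AST is only 2.5 × ULN. If every site reads it that way, nobody is affected. The text is also a journal article, and the operative wording sits in the full protocol and screening forms, which are not shown. Safeguards exist as well: supervised eligibility assessment, an investigator's prescription, adverse-event assessment at each contact, and review by the Data Safety Monitoring Board.

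Much of this stands, and it keeps the weight low. It does not remove the point. The article states the criterion in full and words it so that its plain reading admits the wrong patient, and none of the safeguards says which reading applies.

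Three stronger inferences should be resisted.
- A reader might infer that unsuitable patients have been or will be enrolled. Nothing shows that any site requires both enzymes to be raised.
- A reader might infer a specific liver hazard from the CBD dose. The article states none, and its list of known common cannabinoid adverse events, under Outcomes and assessment tools, has no hepatic item. Nor can absence of on-treatment liver tests be inferred, because the study schedule (Table 1) is not shown.
- A reader might treat the bracket that closes after the bilirubin limit as a second defect in how bilirubin and enzymes combine. It may be only a typesetting slip, and the natural reading is a list of separate markers.

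**Conclusion.** The point holds as a minor safety wording error. As printed, the criterion requires both AST and ALT to reach 3.0 × ULN (5.0 × ULN with liver metastases) before a patient is excluded, so a marked rise in only one does not exclude. This rests on the literal meaning of 'and' in an exclusion list and on the absence of any clarifying text in the article.

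It would be tempting to conclude that the trial's operative eligibility rule is defective. The documents do not support that, because the full protocol may already say 'or' and sites may already apply the limit to each enzyme. The size of the effect cannot be derived from the documents. Sample size, power and the primary analysis are unaffected.

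**What to change.** Reword the item as: *Severe hepatic impairment, defined as any of: total bilirubin ≥ 1.5 × ULN; AST or ALT ≥ 3.0 × ULN (AST or ALT ≥ 5.0 × ULN in patients with liver metastases).* Every threshold stays as it is. The words 'any of' also make plain that bilirubin and the enzymes each suffice.

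First confirm what the full protocol and the screening forms say.
- If they already say 'or', only the article needs correcting.
- If they also say 'and', amend the line by the route the article already describes: "All protocol modifications will be approved by the relevant Human Research Ethics Committee and communicated to all investigators". Then check the baseline liver results already held for enrolled participants, and have the investigator review anyone affected who is still taking study drug. Keep all randomised participants in the analysis.

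The cost is one query and, at most, a one-line amendment and a look at existing results, with no new procedure and no unblinding. The downside is that a few patients who would be eligible under the literal wording become ineligible. Their number cannot be stated from the documents.
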